## Abstract

**Background:**

The number of people with cognitive deficits and diseases, such as stroke, dementia, or attention-deficit/hyperactivity disorder, is rising due to an aging, or in the case of attention-deficit/hyperactivity disorder, a growing population. Neurofeedback training using brain-computer interfaces is emerging as a means of easy-to-use and noninvasive cognitive training and rehabilitation. A novel application of neurofeedback training using a P300-based brain-computer interface has previously shown potential to improve attention in healthy adults.

**Objective:**

This study aims to accelerate attention training using iterative learning control to optimize the task difficulty in an adaptive P300 speller task. Furthermore, we hope to replicate the results of a previous study using a P300 speller for attention training, as a benchmark comparison. In addition, the effectiveness of personalizing the task difficulty during training will be compared to a nonpersonalized task difficulty adaptation.

**Methods:**

In this single-blind, parallel, 3-arm randomized controlled trial, 45 healthy adults will be recruited and randomly assigned to the experimental group or 1 of 2 control groups. This study involves a single training session, where participants receive neurofeedback training through a P300 speller task. During this training, the task’s difficulty is progressively increased, which makes it more difficult for the participants to maintain their performance. This encourages the participants to improve their focus. Task difficulty is either adapted based on the participants’ performance (in the experimental group and control group 1) or chosen randomly (in control group 2). Changes in brain patterns before and after training will be analyzed to study the effectiveness of the different approaches. Participants will complete a random dot motion task before and after the training so that any transfer effects of the training to other cognitive tasks can be evaluated. Questionnaires will be used to estimate the participants’ fatigue and compare the perceived workload of the training between groups.

**Results:**

This study has been approved by the Maynooth University Ethics Committee (BSRESC-2022-2474456) and is registered on ClinicalTrials.gov (NCT05576649). Participant recruitment and data collection began in October 2022, and we expect to publish the results in 2023.

**Conclusions:**

This study aims to accelerate attention training using iterative learning control in an adaptive P300 speller task, making it a more attractive training option for individuals with cognitive deficits due to its ease of use and speed. The successful replication of the results from the previous study, which used a P300 speller for attention training, would provide further evidence to support the effectiveness of this training tool.

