### Objectives

The primary objective of this study is to accelerate P300-based attention training by progressively and optimally adjusting the task difficulty in a training session to each individual using ILC. The proposed iterative learning controller, which determines the task difficulty based on previous performance and task difficulty level, will be compared to the adaptation algorithm used in a previous study by Arvaneh et al [17]. Thus, we will be able to analyze the replicability of Arvaneh et al’s [17] study. A random task difficulty control group will also be used in this study to compare the training effects of personalized approaches with the training effects due to exposure to a range of nonpersonalized task difficulty levels.

While we expect the cognitive enhancements achieved during the training session to be similar among the groups, we expect the experimental group, where the task difficulty is determined by an iterative learning controller, to complete the training session more quickly than the other groups.

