### Procedure

The experimental procedure of this study is based on previous work by Arvaneh et al [17]. An overview of the procedure can be found in Figure 1.

Participants will be asked to fill in a questionnaire at the beginning and end of the experiment. They will then complete a continuous random dot motion (RDM) task, which will serve as a baseline for their cognitive abilities. Afterward, participants will receive attention training using a P300 speller task, where the task difficulty in each run of the speller is either chosen randomly (control group 2) or adjusted to the participant’s performance (control group 1 and experimental group). To analyze improvements in cognitive abilities, participants are asked to complete the RDM task again after the training.

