#### RDM Task

The continuous RDM task is based on Arvaneh et al [17] and Kelly and O’Connell [33]. In this task, the participants will focus on moving dots on the screen, which transition from incoherent motion to coherent motion. During incoherent motion, all dots will continuously move in random directions, whereas in coherent motion, a significant fraction of the dots will move in one direction, either left or right. The participants will be asked to indicate the direction of the coherent motion by pressing the left or right arrow key once they are sure of the motion direction. In both the pre- and posttraining phases, the main task consists of 40 trials, where the coherence level, that is, the fraction of coherently moving dots, and the motion direction vary in each trial.

An average of 118 dots, with a size of 6×6 pixels each, are displayed in a circular aperture of 5° at a viewing distance of 70 cm, resulting in a dot density of approximately 10.8%. Each dot is black against a grey background. The dots are moving at a speed of 3.33°/second. The incoherent motion lasts for either 3.1, 4.2, or 5.7 seconds, and the coherent motion always lasts for 1.9 seconds. The coherence level is either 19% or 25%.

To allow participants to understand the task, a practice session will be carried out before the pretraining phase. The practice session consists of 3 blocks of 6 trials each. In the first block, the coherence levels are either 60% or 80%, reducing to 30% or 40% in the second block, and finally reaching 20% or 25% in the last block of the practice session. All other parameters of the task are the same as above. During the practice session, participants will receive verbal feedback on hits, misses, and false alarms.

The code for this task was developed in-house using PsychoPy [34] and the stimuli are presented on a 52.7-cm-wide LED monitor with a refresh rate of 60 Hz and a resolution of 1920×1080 pixels.

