##### Training Phase

During the training phase, all participants will copy-spell the word “beautiful” for 5 runs. Ten flashes per row and column are used for the first run of the training phase, for all groups. The number of flashes in all subsequent runs is adapted randomly (control group 2) or based on the participants’ performance in the previous run (control group 1 and experimental group). The participants in all groups will receive feedback but will not be told why the number of flashes varies in each run.

The details of the task difficulty adaptation for each group are described below:

*Control group 1*: The adaptation algorithm in control group 1 is a replication of the work described in [17]. The number of flashes in each run, *N_i_*, is the average of the minimum number of flashes needed to reach more than 66% spelling accuracy in the previous run, referred to as *N*_(*i*–1)66_, and the actual number of flashes used in the previous run, *N*_*i*–1_, that is,

where *N_i_* is rounded to the nearest integer. If the spelling accuracy in the previous run was below 66%, then the number of flashes in the next run is increased by 1, that is,

*N_i_*=*N_i_*_–1_ + 1. **(5)**

*Control group 2*: The task difficulty adaptation of control group 2 is not based on the participants’ performance. Instead, the number of flashes in each run is chosen at random between 1 and 10 flashes. Choosing the number of flashes in this way will expose the participants in control group 2 to varying task difficulties in an unpredictable way. This allows the authors to compare the personalized adaptation approaches of the other 2 groups to a nonadaptive difficulty adjustment approach under similar conditions. Using a constant task difficulty in this group would potentially lead to differences due to an easier average task difficulty [36] and reducing the number of flashes by the same amount each run would introduce predictability, which the other groups do not have.

*Experimental group*: In the experimental group, a P-type ILC controller is used to adapt the number of flashes in the next run, *N_i_*, based on the number of flashes and error in the previous run, *N_i_*_–1_ and *e_i_*_–1_=1-*J*_1(
*i*–1)_ (where *J*_1_ is the spelling accuracy). The update law of the controller is

*N_i_*=*N_i_*_–1_+ϵ*f*(*e_i_*_–1_), **(6)**

where ε is a controller parameter and

*f*(*e*_i–1_)=2*e_i_*_–1_–1. **(7)**

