## Results

This study was approved by the Maynooth University Ethics Committee (BSRESC-2022-2474456) and is registered on ClinicalTrials.gov (NCT05576649). Participant recruitment and data collection began in October 2022. We expect to publish the results in 2023. This study is replicating the experimental protocol of Arvaneh et al [17], comparing their task difficulty adaptation approach to a novel approach using an iterative learning controller, as well as random task difficulty levels in each run.

Arvaneh et al [17] showed a significant enhancement of ERP components and performance in the RDM task after the P300 speller training, suggesting that participants’ attention improved. We expect such an improvement for all groups in this study, with changes in the length of the training between groups due to the different adaptation approaches.

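### Every arm is trained, so within-arm pre-post change on the random dot motion task cannot show that the training transfers

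*Protocol article*

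**What the plan says.** **Who is trained.** Under Training Phase: "During the training phase, all participants will copy-spell the word" chosen for that phase, in five runs. The Abstract (Methods) states what separates the arms: "Task difficulty is either adapted based on the participants" and their performance (experimental group, control group 1), or is random (control group 2). The Objectives give the purpose of the random arm: to "compare the training effects of personalized approaches with the training effects due to exposure to a range of nonpersonalized task difficulty levels". It is a trained arm too.

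**What the RDM task is for.** The Abstract (Methods) has it done before and after training "so that any transfer effects of the training to other cognitive tasks can be evaluated". The Procedure section says: "To analyze improvements in cognitive abilities, participants are asked to complete the RDM task again after the training". Under Tasks and Stimuli, RDM Task: "In both the pre- and posttraining phases, the main task consists of 40 trials". A practice session of 3 blocks of 6 trials comes before the first of these. The RDM paragraph of Data Analysis plans between-group tests and within-group tests such as the paired t test, for accuracy and mean response time.

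**What is expected and concluded.** The Objectives expect similar cognitive gains among the groups. The Results section recalls the enhanced event-related potentials (ERPs) and RDM performance of the earlier study and adds: "We expect such an improvement for all groups in this study". According to the Abstract (Conclusions), successful replication "would provide further evidence to support the effectiveness of this training tool".

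**Limitations.** These name the single session, the short training and a healthy, probably young sample. They do not mention retest effects or the lack of an untrained comparator.

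**The concern.** A within-arm pre-post test asks whether RDM performance changed over the session. The plan wants to know whether the training changed it. The two questions coincide only if nothing else moves RDM performance between the two tests, and the design has no arm that could show this.

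The randomized contrasts do not fill the gap, because they compare one way of setting difficulty with another. The authors also expect no cognitive difference between groups. On their own prediction, the RDM evidence for transfer would therefore come entirely from the uncontrolled within-arm changes. At stake is a published statement that the training transfers to another cognitive task, when the same data could arise without any transfer.

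**Working it through.** **1. What each comparison estimates.** Write the mean RDM change in arm g as

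change(g) = T(g) + R,

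where T(g) is the effect of that arm's training and R is the net effect of repeating the task, fatigue and time, which would occur without training.

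- The within-arm test estimates T(g) + R. The two parts cannot be separated, because no arm has T = 0 by design.
- The between-arm contrast estimates T(g) − T(h), and R cancels. This is valid for the adaptation method but does not address training against no training.
- In the expected result, all arms change by the same amount c. That fits T = c with R = 0, T = 0 with R = c, and any split between them.

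This conclusion needs no figure for R.

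**2. Inputs for an illustration.**

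- Arm size n = 15, total 45 (Participants section). The plan's recruitment figure reproduces: 45 / 0.9 = 50.
- Test: paired t test within arm (Data Analysis, RDM Task).
- Assumed, since the document gives neither: two-sided alpha 0.05, and a net practice gain d of 0.2, 0.3 or 0.5 SD of the paired difference.
- Training effect set to zero.

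**3. Formula.** The paired t statistic follows a noncentral t distribution with n − 1 = 14 degrees of freedom and noncentrality d × √n. The probability of significance is P(|t| > 2.145), where 2.145 is the two-sided 5% critical value on 14 degrees of freedom.

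| Assumed d | Noncentrality d × √15 | Probability that one arm is significant |
|---|---|---|
| 0 | 0 | 5% |
| 0.2 | 0.77 | 11% |
| 0.3 | 1.16 | 19% |
| 0.5 | 1.94 | 44% |

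**4. The between-arm test under the same assumption.** A simulated one-way ANOVA on change scores (3 × 15 participants, 20,000 runs) with the same practice gain in every arm rejects in 5.0% of runs at d = 0, 5.1% at 0.5 and 5.0% at 0.8. The randomized comparison keeps its error rate.

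**The case against.** **The primary aim does not depend on this.** The aim is to accelerate training, tested as a between-arm comparison of total flashes in runs 2-5. This stands in full.

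**The effectiveness sentence is not about the RDM task alone.** A reader might infer that the whole effectiveness claim rests on RDM change, or that the expected pattern is just what practice would give. The document does not support either reading. The Abstract's Conclusions speak of the earlier results in general, and the Results section counts ERP enhancement among them. Repeating the RDM task does not explain a change in ERP or alpha power during the speller. Those ratios are also pre-post measures, and the planned EEG-RDM correlation does not isolate training. But this point is about RDM transfer and makes no case about the EEG measures.

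**The practice session counts in the plan's favour.** The 3 × 6 = 18 trials come before baseline, include verbal feedback, and step down to 20% or 25% coherence, close to the 19% or 25% tested. They should reduce early learning. They cannot remove or measure what remains, and 40 further trials follow before training begins.

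**The net bias may not be positive.** The session may last up to 2 hours, and the questionnaire asks about tiredness, alertness, boredom and eye strain. Fatigue could lower the second RDM score and hide a real transfer. This stands: the size and sign of R are unknown.

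**Larger probabilities can be computed.** At d = 0.5, at least one of three arms is significant with probability 1 − (1 − 0.438)³ = 82%, and a pooled test of 45 with 91%. Neither is a decision rule in the protocol, so neither measures the plan's error rate.

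**The earlier study may have had an untrained control.** That cannot be checked from the document. It would not add such a control to this trial.

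**Conclusion.** The point holds for within-arm RDM change. Because every arm is trained, that change cannot show transfer of the training or training-induced cognitive improvement, and equal gains in all arms would not distinguish training from retest. This follows from the design and rests on no assumed number.

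The 11%, 19% and 44% are illustrations under assumed practice gains of 0.2, 0.3 and 0.5 SD with no training effect; they are not estimates for this trial. Fatigue could make the net bias smaller or reverse it.

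The comparison of training length and all randomized between-arm contrasts remain valid for the adaptation method. A statistical analysis plan could restrict the inference but could not supply the missing comparator, and the article itself states the inference, so the correction belongs in the article's wording.

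**What to change.** 1. In the Abstract (Methods), the Procedure section and the RDM paragraph of Data Analysis, state that within-arm RDM change is uncontrolled and descriptive and is not evidence of transfer.
2. Reserve causal statements for the randomized between-arm contrasts, and say that these concern the adaptation method.
3. In the Abstract (Conclusions) and the Results section, say that the RDM part of a replication shows only whether the pre-post change was reproduced, not that the training caused it.
4. Add to Limitations that there is no untrained comparator, and that repetition, fatigue and time may account for RDM change in either direction.
5. Optionally, report the trend across the 40 pretraining trials, as description only. It mixes learning, fatigue and trial mix and cannot measure the gain from first to second test.

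The cost is a few sentences and a weaker claim about RDM transfer; no further participants are needed. An untrained arm that repeats the RDM task after the same interval would address the question directly, but recruitment has begun and 15 per arm would be too few: for an assumed difference in change of 0.5 SD, power is 26%, and 80% power needs about 63 per arm (normal approximation).

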**Trial Registration:**

ClinicalTrials.gov NCT05576649; https://clinicaltrials.gov/ct2/show/NCT05576649

**International Registered Report Identifier (IRRID):**

DERR1-10.2196/46135

## Introduction

### Background

Cognition includes many facets of complex processing functions, such as, and not limited to, attention, the acquirement of knowledge, memory, decision-making, and comprehension [1]. Cognitive deficits often present as symptoms in many underlying neurological disorders.

In the aging population, cognitive decline is common, however, can be accelerated by neurodegenerative diseases, such as dementia, or through brain trauma and stroke. Furthermore, the increased prevalence of cognitive deficits is apparent in every age demographic. As a result of the COVID-19 pandemic, many long-term neurological effects have been identified in patients who have experienced COVID-19 infection. In a study published by Hartung et al [2], it was identified that of a sample group of 969 patients, approximately 26% of patients experience mild cognitive impairment in the aftermath of the infection. Other cognitive diseases, such as attention-deficit/hyperactivity disorder (ADHD) and autism spectrum disorder, are common neurocognitive disorders that are identified in children. All these diseases feature a profound effect on the quality of life of the individual because of impairments in cognition [3-5].

The common treatments for these conditions are pharmacological interventions or therapeutic interventions. However, these disorders have no known cure, and rather, treatments are created to alleviate the symptoms of the disorder.

Pharmacological interventions, such as the use of psychostimulant medicines, have been rendered highly effective in treating symptoms of cognitive deficits. However, they have been criticized for the adverse effects which can occur due to their use [6]. Methylphenidate and lisdexamfetamine are 2 common psychostimulants used in the treatment of a variety of cognitive disorders, including ADHD. Both stimulants have shown to be efficacious in the treatment of the symptoms associated with the disorder but can result in insomnia, decreased appetite, headaches, and abdominal pain [7].

Cognitive disorders and their interventions, both pharmacological and nonpharmacological, can be highly costly, not only for the individual but also for health care systems globally [8,9]. This can cause great distress for individuals, as diagnosis and treatment for cognitive disorders can become inaccessible, as well as immense pressure on health care systems due to the increasing burden of these diseases. For these reasons, there is a clear need for low-cost and effective treatments for neurocognitive disorders.

### Neurofeedback Training

Electroencephalographic neurofeedback (EEG-NFB) is a type of brain-computer interface (BCI), which provides real-time feedback to the individual based on neural signals of interest as measured by electroencephalography (EEG), thus training the individual to self-regulate their brain activity [10]. EEG-NFB was introduced in the 1960s independently by Nowlis and Kamiya [11], and Sterman et al [12], and was commonly referred to as EEG biofeedback. Nowlis and Kamiya [11] presented data to confirm that patients could control their brain activity as a result of engaging with rewards using an EEG measuring device. Sterman et al [12] discovered through training cats that they too could modulate brain wave activity. As a result of these discoveries, a variety of treatments have been developed to alleviate symptoms of many cognitive disorders, including ADHD, schizophrenia, and many others [13-15].

Due to criticism relating to the efficacy of EEG-NFB in the 1970s, there was a decline in research on the use of EEG-NFB [16]. However, in recent years there has been a reemergence of the use of EEG-NFB globally in many research and clinical settings [10].

One example of a novel EEG-NFB is the adaptive P300 speller for attention training by Arvaneh et al [17]. The P300 speller was first introduced by Farwell and Donchin [18] in 1988 as a tool for patients who could not communicate, such as in the case of patients who have “locked-in” syndrome. In the speller, a matrix of symbols (eg, letters and numbers) is presented to the user. Each row and column in the matrix of symbols is highlighted or flashed in random order. When the user only focuses on the flashes of a target symbol and ignores the other flashes, the BCI can select this target symbol by identifying the row and column that elicited a P300 wave, thus allowing the user to spell words with their mind. In this process, each row and column are flashed several times, so that the signal-to-noise ratio (SNR) of the EEG signals can be increased by averaging. Usually, this number of flashes per row and column is fixed to allow the user to spell words sufficiently well in an acceptable amount of time. However, Arvaneh et al [17] progressively reduced the number of flashes in a training session based on the user’s performance to intentionally decrease the SNR. This makes it more difficult for the user to spell words correctly, thus encouraging them to improve their focus in order to maintain their performance. The researchers demonstrated that a single training session on healthy adults resulted in an increase in performance in a cognitive task, as well as an enhancement of event-related potentials (ERPs) [17].

This study intends to replicate the experiment by Arvaneh et al [17], comparing their adaptation of the number of flashes to a novel adaptation approach based on iterative learning control (ILC).

